## Abstract

**Background:**

Vascular endothelial dysfunction, arteriosclerosis and atherosclerotic plaque are well-known risk factors for cardiovascular disease (CVD). Studies on vascular health markers have been well-established, however, there is still a lack of related research on combined vascular structure and function indicators.

**Method:**

Beijing vascular health stratification (BVHS) is an evaluation system aiming at vascular health, combined the endothelial function, arteriosclerosis, atherosclerotic plaque and vascular lumen stenosis to comprehensively assess the vascular health and grade it. This study will explore the predictive value of the combined evaluation of vascular structure and function for cardiovascular events and assess the predictive value of BVHS and compare it with the existing risk assessment systems. A total of 1500 subjects will be enrolled into the prospective cohort study from a community and will be followed up for at least 3 years from July 1, 2020 to June 30, 2023. Subjects aged 40 or above, without coronary heart disease, stroke or peripheral artery disease, with written informed consent will be included; subjects with end-stage hepatorenal diseases (uremia, renal failure, cirrhosis, liver failure), mental disorders or cognitive disorders, with any other factors that the researcher thinks are not suitable for the study will be excluded. Traditional cardiovascular risk factors will be collected as adjusted confounders.

**Discussion:**

BVHS is a potential and scientific vascular health evaluation system. The study will be the first to grade vascular health by combing various vascular indicators and explore the prediction value and compare with other risk prediction system in general Chinese population.

*Trial registration*: The trial is registered on http://www.chictr.org.cn/ (ChiCTR2000034085).

## Background

Vascular health indicators, including lumen stenosis and dysfunction, both reflect the long-term cumulative effects of traditional and unidentified cardiovascular (CV) risk factors before and after clinical vascular events, and can be regarded as an alternative end point indexes for target organ damage and risk prediction [1]. Several markers have been considered as the reflection of vascular health, among them endothelial function, arterial stiffness and carotid atherosclerosis are the most common indicators [1]. Endothelial dysfunction may represent the effect of traditional CV risk factors on vascular health [2]. Arterial stiffness is increasingly recognized as a surrogate end point for cardiovascular disease (CVD) and as a risk factor for clinical hypertension [3, 4]. Carotid ultrasound measurement of intima-media thickness (IMT) along with carotid plaque are emerging as the focus of carotid artery ultrasound imaging for CV risk prediction [5]. Currently, studies on assessing vascular health use only one or more of these indicators [6–8]. Beijing Vascular Health Stratification (BVHS) was put forward to assess vascular health including all stages of vascular disease progression, from endothelial function to arteriosclerosis to vascular stenosis [9]. BVHS is a risk prediction tool using subclinical vascular measures such as endothelial function, arterial stiffness, carotid atherosclerotic plaques and artery stenosis by non-invasive detections. Furthermore, traditional risk factors are not included in BVHS, but are used as adjusted confounding factors to analyze the independent predictive role of BVHS.

All the markers are graded as artery functional injury or structural disease or both. Our previous retrospective study found that the BVHS was a comprehensive risk assessment system and was independent of traditional CV risk factors [10]. However, the previous study did not develop a strict study design and follow-up plan. Therefore, this study was designed as a prospective cohort study to verify the previous research results and further explore the clinical value of BVHS for the prediction of major adverse cardiovascular events (MACEs).

## Aim

BVHS Study is designed to answer two important clinical questions: (1) A preliminary study on the value of BVHS in predicting MACEs independently of traditional CVD risk factors; and (2) A preliminary comparative study on the predictive value of BVHS and other risk prediction system model of CVD commonly used at home and abroad, such as the China-PAR Project [11] and the Pooled Cohort Equations [12].

## Methods

### Study design (Fig. 1)

**Fig. 1 Fig1:**
[figure not shown]
Study design. BVHS, Beijing Vascular Health Stratification; MACEs, major adverse cardiovascular events

BVHS is a prospective cohort study which will enroll 1500 participants from Jindingjie community health service center in western Beijing, China. The biggest advantage of the community population is that the participants are permanent residents of the area, have good compliance, and are easy to carry out follow-up studies.

The study design is showed in Fig. 1.

### Participants population, inclusion and exclusion criteria

Participants without CVD from Jindingjie community health service centers will be recruited by their site-specific responsible physicians.

Subjects aged 40 or above, without coronary heart disease, stroke or peripheral artery disease, with written informed consent will be included; subjects with liver disease (hepatic jaundice, cirrhosis or liver failure), chronic kidney disease (estimated Glomerular Filtration Rate, eGFR < 60 mL/min per 1.73 m^2^), mental disorders or cognitive disorders, with any other factors that the researcher thinks are not suitable for the study such as non-local residents or life expectancy less than one year will be excluded.

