### Baseline demographics, physical examinations and data collection

Case record form (CRF) and electronic data capture (EDC) are used for data collection and data management. The personal information of all participants will be deprivileged.

Data collected at the baseline will include participants’ demographics including date of birth, gender, education, occupation, and health insurance, lifestyles including tobacco smoking, alcohol drinking, diet pattern (food frequency), and time on sedentary life, systolic blood pressure (SBP), diastolic blood pressure (DBP), heart rate, height, weight; medical history of hypertension, diabetes mellitus and hyperlipidemia, and current use of medications (statins, aspirin/clopidogrel, angiotensin converting enzyme inhibitors/angiotensin receptor blocker, β-receptor blocker, calcium channel blockers, insulin, hypoglycemic medicine, and nitrates). Blood pressure and heart rate were measured by pulse wave sphygmomanometer (RBP-9000c, Shenzhen, China) for 3 times after 30 s interval. Baseline laboratory blood parameters to be collected include total cholesterol (TC), triglyceride (TG), low density lipoprotein cholesterol (LDL-C), high density lipoprotein cholesterol (HDL-C), C-reactive protein (CRP), homocysteine (HCY), uric acid, urea nitrogen, creatinine, fasting plasma glucose (FPG), alanine aminotransferase (ALT), aspartate aminotransferase (AST), total protein, albumin, lactate dehydrogenase, hydroxybutyric acid, creatine kinase, creatine kinase isoenzyme.

Hypertension is defined as SBP ≥ 140 mmHg or DBP ≥ 90 mmHg or current use of anti-hypertension medications. Diabetes mellitus is defined as either glycosylated hemoglobin (HbA1c) ≥ 6.5% or FPG ≥ 126 mg/ dL (7.0 mmol/L) or 2-h plasma glucose ≥ 200 mg/dL (11.1 mmol/L) during an oral glucose tolerance test; or currently taking blood glucose lowering medications or insulin. Hyperlipidemia includes the following: TC > 200 mg/dL/(5.18 mmol/L); or LDL-C ≥ 130 mg/dL (3.37 mmol/L); or HDL-C < 40 mg/dL (1.04 mmol/L) in men and < 50 mg/dL (1.30 mmol/L) in women; or lipoprotein a > 50 mg/dL (125 nmol/L), or persistent elevations of TG ≥ 175 mg/dL (≥ 1.97 mmol/L); or currently receiving antilipidemic medications.

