### End points and assessment

The primary outcome will be the incidence of MACEs.

MACEs include all cause death, cardiovascular death, non-cardiovascular death, undetermined cause of death, myocardial infarction (MI), hospitalization for unstable angina (UA), transient ischemic attack (TIA) and stroke, heart failure (HF) event, percutaneous coronary intervention (PCI), coronary artery bypass grafting (CABG), peripheral vascular intervention (PVI), stent thrombosis [16].

Cardiovascular death includes acute MI, sudden cardiac death, heart failure, stroke, cardiovascular procedure and cardiovascular hemorrhage etc.

Definition of MI is clinical syndrome where there is evidence of myocardial necrosis in a clinical setting consistent with acute myocardial ischemia, including presence of acute symptoms of myocardial ischemia, such as chest, upper extremity, mandibular, or epigastric discomfort, or an ischemic equivalent such as dyspnea or fatigue; presence of new or presumed new significant ST-segment-T wave (ST-T) changes or new left bundle-branch block (LBBB) consistent with acute myocardial ischemia; presence of new or presumed new pathological Q waves consistent with MI; presence of thrombus in a major epicardial vessel consistent with an acute MI; demonstration of a new change in myocardial viability or function consistent with MI; occurrence of an adverse angiographic finding during PCI consistent with acute myocardial ischemia; angiographic documentation of a new CABG or new native coronary artery occlusion within 48 h of CABG surgery; cardiac biomarker level [16].

Definition of hospitalization for UA include unscheduled hospitalization for the management of UA, occurring within 24 h of the most recent symptoms. Hospitalization is defined as an admission to an inpatient unit or a visit to an emergency department (ED) that results in at least a 24-h stay (or a change in calendar date if the hospital admission or discharge times are not available) [16].

Stroke is defined as an acute episode of focal or global neurological dysfunction caused by brain, spinal cord, or retinal vascular injury as a result of hemorrhage or infarction. Categorical description of stroke type classified into 1 of 3 mutually exclusive categories (ischemic, hemorrhagic, undetermined) [16].

TIA is defined as transient episode of focal caused by brain, spinal cord, or retinal ischemia without acute infarction [16].

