HF event is defined as presentation of the patient for an urgent, unscheduled clinic/office/ED visit or hospital admission, with a primary diagnosis of HF, where the patient exhibits new or worsening symptoms of HF on presentation, has objective evidence of new or worsening HF, and receives initiation or intensification of treatment specifically for HF [16].

PCI is the placement of an angioplasty guidewire, balloon, or other device (e.g. stent, atherectomy, brachytherapy, or thrombectomy catheter) into a native coronary artery or CABG for the purpose of mechanical coronary revascularization [16].

CABG surgery is a procedure performed to bypass partially or completely occluded coronary arteries with veins and/or arteries harvested from elsewhere in the body, thereby improving the blood supply to the coronary circulation supplying the myocardium (heart muscle) [16].

A PVI is a catheter-based or open surgical procedure designed to improve arterial or venous blood flow or otherwise modify or revise vascular conduits. Procedures may include, but are not limited to, percutaneous transluminal balloon angioplasty, stent placement, thrombectomy, embolectomy, atherectomy, dissection repair, aneurysm exclusion, treatment of dialysis conduits, placement of various devices, intravascular thrombolysis or other pharmacotherapies, and open surgical bypass or revision [16].

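### The entry criteria name fewer cardiovascular conditions than the primary endpoint counts: heart failure and TIA are not listed at entry, yet a worsening or a repeat counts as an incident MACE

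*Protocol article*

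**What the plan says.** The section on participants and criteria opens with a general statement: "Participants without CVD from Jindingjie community health service centers will be recruited by their site-specific responsible physicians". CVD is not defined there or elsewhere in the article. The criteria follow: "Subjects aged 40 or above, without coronary heart disease, stroke or peripheral artery disease, with written informed consent will be included". The abstract gives the same three diseases: "without coronary heart disease, stroke or peripheral artery disease, with written informed consent will be included". The exclusions then cover liver disease, kidney disease, and mental or cognitive disorders. They end with a discretionary clause: "with any other factors that the researcher thinks are not suitable for the study such as non-local residents or life expectancy less than one year".

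Under End points and assessment, "The primary outcome will be the incidence of MACEs". The components include "transient ischemic attack (TIA) and stroke, heart failure (HF) event". An HF event is an urgent visit or admission "where the patient exhibits new or worsening symptoms of HF on presentation", with objective evidence and treatment that is started or stepped up. The TIA definition describes a transient ischaemic episode and does not require it to be the participant's first.

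The baseline section lists "medical history of hypertension, diabetes mellitus and hyperlipidemia, and current use of medications".

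**The concern.** The study asks whether Beijing Vascular Health Stratification (BVHS) predicts MACEs, and how it compares with existing risk scores. For events to be incident, participants should be free at baseline of the conditions later counted. For HF and TIA the listed criteria do not secure this. Someone with non-ischaemic HF or a past TIA meets every named criterion. A later decompensation or second TIA is then credited as a predicted event, although the condition was present when the vessels were examined.

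If such people tend to have worse vascular grades and also more events, the Cox hazard ratio and the C statistic would partly reflect recurrence in people already known to be ill. The same events would enter the comparison with the other risk models. The plan expects only about 45 events, so a handful matters.

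**Working it through.** **Step 1. Entry list against endpoint.**

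- Coronary heart disease: must be absent at entry; the endpoint counts MI, hospitalised unstable angina, PCI and CABG.
- Stroke: must be absent at entry; the endpoint counts stroke.
- Peripheral artery disease: must be absent at entry; the endpoint counts peripheral vascular intervention.
- TIA: not named at entry; the endpoint counts any TIA.
- HF: not named at entry; the endpoint counts HF events, including worsening of existing HF.

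The first three match. The last two do not, unless the undefined term CVD is read to cover them.

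**Step 2. The plan's own event figure.** Inputs from the section on incidence of end point events: coronary heart disease 497 and stroke 533 per 100,000 per year, over 3 years.

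- 3 × (497 + 533)/100,000 = 0.0309, which the plan rounds to 30 per 1000.
- 1500 × 0.030 = 45.0 (unrounded: 1500 × 0.0309 = 46.4). The stated figure of about 45 reproduces.
- The Results section reports 1648 enrolled: 1648 × 0.0309 = 50.9 events on the same rates.

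**Step 3. Events from pre-existing HF or TIA.** The documents give neither the prevalence nor the event risk, so both are assumed: prevalence 1% to 2%, and a 15% to 30% risk of an HF or cerebrovascular event during follow-up.

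- People: 0.01 × 1648 = 16.5; 0.02 × 1648 = 33.0.
- Events: 16.5 × 0.15 = 2.5; 33.0 × 0.30 = 9.9.

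**Step 4. Share of all events.** The 50.9 rests on coronary and stroke incidence only, so these events are added to it.

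- Low: 2.5/(50.9 + 2.5) = 2.5/53.4 = 4.6%, about 5%.
- High: 9.9/(50.9 + 9.9) = 9.9/60.8 = 16.3%, about 16%.

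**Step 5. Wider assumptions.** Take the planned 1500, with prevalence 0.5% to 3% and risk 10% to 30%, and a 3% event risk in the remainder.

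- Low: 1500 × 0.005 × 0.10 = 0.8 events, against 1500 × 0.995 × 0.03 = 44.8 others: 1.6%, about 2%.
- High: 1500 × 0.03 × 0.30 = 13.5 events, against 1500 × 0.97 × 0.03 = 43.6 others: 23.6%, about 24%.

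Two features make these shares generous. Deaths from other causes, procedures, and first HF and TIA events would enlarge the denominator. The numerator also includes a first stroke after a past TIA, which is not a repeat of the baseline condition.

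**The case against.** The strongest reply is that the listed diseases are not the whole rule. The sentence just before them limits recruitment to people without CVD. On an ordinary reading that bars known HF and arguably TIA, and the researcher may exclude for other reasons. This stands in part: the documents do not support saying that the plan admits such people without qualification. It does not settle the matter, because the term is undefined and the next sentence spells out three diseases, which a recruiting physician could take as its meaning. The examples attached to the discretionary clause do not point to HF or TIA.

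A reader might also infer from the baseline history list that prior HF or TIA was never recorded and cannot be removed later. That does not follow. The list also leaves out coronary disease, stroke and peripheral artery disease, which must have been checked to apply the criteria, so it is not exhaustive. Table 1 has a baseline questionnaire and an eligibility check whose contents are not shown.

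A reader might put the size at up to 22% by dividing 9.9 by 45. That sets events among 1648 people against events expected in 1500, and it is a ratio rather than a share.

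Finally, no passage shows that people with prior HF or TIA fall in the higher BVHS grades. Inflation of the hazard ratio is plausible but not demonstrated, which is why the wording here is that it may be distorted.

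**Conclusion.** The point holds as an inconsistency to be reconciled. An undefined CVD-free population stands beside a three-disease list that is narrower than the primary endpoint. Under the list, a decompensation of existing HF or a repeat TIA counts as an incident MACE.

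The size cannot be derived from the documents. The 5% to 16% rests on the assumed prevalence and risk, and on the plan's 3-year coronary and stroke rates applied to 1648 people. Wider assumptions give 2% to 24%. The direction and amount of any bias in the hazard ratio or C statistic are not established. The issue is still worth correcting, because expected events are few and the correction is cheap.

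**What to change.** 1. In the participants section, define the CVD-free population to match the endpoint: no history, before the baseline vascular examination, of coronary heart disease, stroke, TIA, heart failure or peripheral artery disease.
2. Enrolment ended in October 2020, so a new criterion cannot change who entered. Ascertain pre-baseline HF and TIA through the medical documents and the telephone or clinic contacts that the follow-up section already provides for. Do this in the same way for every participant, whatever the BVHS grade or later events.
3. Exclude participants found to have either condition from the primary incident-MACE analysis and from the comparison with the other risk models. Report the full cohort as a sensitivity analysis.

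The cost is two extra history items to abstract, and the loss of perhaps 16 to 33 participants and a few events on the assumptions above. The gain is that the primary endpoint becomes incident for these two components.

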### Baseline demographics, physical examinations and data collection

Case record form (CRF) and electronic data capture (EDC) are used for data collection and data management. The personal information of all participants will be deprivileged.

Data collected at the baseline will include participants’ demographics including date of birth, gender, education, occupation, and health insurance, lifestyles including tobacco smoking, alcohol drinking, diet pattern (food frequency), and time on sedentary life, systolic blood pressure (SBP), diastolic blood pressure (DBP), heart rate, height, weight; medical history of hypertension, diabetes mellitus and hyperlipidemia, and current use of medications (statins, aspirin/clopidogrel, angiotensin converting enzyme inhibitors/angiotensin receptor blocker, β-receptor blocker, calcium channel blockers, insulin, hypoglycemic medicine, and nitrates). Blood pressure and heart rate were measured by pulse wave sphygmomanometer (RBP-9000c, Shenzhen, China) for 3 times after 30 s interval. Baseline laboratory blood parameters to be collected include total cholesterol (TC), triglyceride (TG), low density lipoprotein cholesterol (LDL-C), high density lipoprotein cholesterol (HDL-C), C-reactive protein (CRP), homocysteine (HCY), uric acid, urea nitrogen, creatinine, fasting plasma glucose (FPG), alanine aminotransferase (ALT), aspartate aminotransferase (AST), total protein, albumin, lactate dehydrogenase, hydroxybutyric acid, creatine kinase, creatine kinase isoenzyme.

Hypertension is defined as SBP ≥ 140 mmHg or DBP ≥ 90 mmHg or current use of anti-hypertension medications. Diabetes mellitus is defined as either glycosylated hemoglobin (HbA1c) ≥ 6.5% or FPG ≥ 126 mg/ dL (7.0 mmol/L) or 2-h plasma glucose ≥ 200 mg/dL (11.1 mmol/L) during an oral glucose tolerance test; or currently taking blood glucose lowering medications or insulin. Hyperlipidemia includes the following: TC > 200 mg/dL/(5.18 mmol/L); or LDL-C ≥ 130 mg/dL (3.37 mmol/L); or HDL-C < 40 mg/dL (1.04 mmol/L) in men and < 50 mg/dL (1.30 mmol/L) in women; or lipoprotein a > 50 mg/dL (125 nmol/L), or persistent elevations of TG ≥ 175 mg/dL (≥ 1.97 mmol/L); or currently receiving antilipidemic medications.

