## Results

BVHS is a potential and scientific vascular health evaluation system. The study will be the first to grade vascular health by combing various vascular indicators and explore the prediction value and compare with other risk prediction system in general Chinese population.

The baseline characteristics of study participants were showed in Table 2. From May 2020 to October 2020, a total of 1648 participants were enrolled in the study. Mean age was 60.27 ± 6.71 years, 33.9% were male. Hypertension was found in 39.3% of participants. About 19.3% were diabetes, while dyslipidemia was observed in 41.7% and 37.4% were on medication of statins. Smoking was reported by 27.1% of participants.

**Table 2 Tab2:** Baseline characteristics of study participants

Variables	N	%
Age group		
< 65 years	1190	72.2
≥ 65 years	458	27.8
Sex, male	558	33.9
Hypertension	647	39.3
Diabetes mellitus	318	19.3
Dyslipidemia	687	41.7
Use of statins	615	37.4
Smoker	447	27.1

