A substantial global burden of carotid atherosclerosis exists. In people aged 30–79 years in 2020, the global prevalence of increased CIMT is estimated to be 27.6% (95% CI 16.9–41.3); of carotid plaque is estimated to be 21.1% (13.2–31.5); and carotid stenosis is estimated to be 1.5% (1.1–2.1) [24]. Carotid plaque and carotid stenosis are easily detected with duplex ultrasound because of the superficially positioned carotid artery. CIMT and plaque consensus suggested a standard for carotid image acquisition [13, 14]. People with carotid atherosclerosis are classified by the European Society of Cardiology as having a very high risk of death from CVD [25]. Advanced carotid atherosclerosis, defined as 50% or more stenosis, increases risk of CVD and carotid lesion-derived stroke [26].

CVD risk-assessment tools and appropriate recommendations for risk assessment in clinical guidelines are essential for implementation of a high-risk CVD prevention strategy in a population [12, 27]. Most guidelines and risk assessment models are focused on traditional CV risks, such as age, sex, SBP or hypertension, TC or ratio of TC to HDL cholesterol, smoking, HDL cholesterol, obesity, diabetes mellitus and family history of premature CVD or coronary heart disease (CHD) [27]. Although several well-known models and algorithms for CVD risk assessment have been developed [11, 27, 28], these models and guideline recommendations might not be suitable for direct application in clinical practice. In addition, an analysis of 5 risk scores, 4, including the American Heart Association (AHA) and American College of Cardiology (ACC) atherosclerotic cardiovascular disease (ASCVD) risk score, showed overestimation of risk (25% to 115%) in a modern, multiethnic cohort without baseline clinical ASCVD. If validated, overestimation of ASCVD risk may have substantial implications for individual patients and the health care system [29]. CVD risk assessment depends not only on risk-factor profile, but also on the direct vascular health risk levels, and relative risk of each vascular health factor.

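### Diabetes and hyperlipidemia are defined partly by tests the plan does not list, and without the recorded history it collects; the definitions, Table 2 and the Aim 1 adjustment set need aligning

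*Protocol article*

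**What the plan says.** All references are to the Protocol article.

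- **Diabetes** (Baseline demographics, physical examinations and data collection): the definition opens with "Diabetes mellitus is defined as either glycosylated hemoglobin (HbA1c", using a cut-off of 6.5%. The alternatives are an FPG of at least 7.0 mmol/L, a 2-hour value of at least 11.1 mmol/L on a glucose tolerance test, and current glucose-lowering treatment.
- **Hyperlipidemia** (same section): raised TC, raised LDL-C or low HDL-C, "or lipoprotein a > 50 mg/dL (125 nmol/L), or persistent elevations of TG" at or above 1.97 mmol/L, or current lipid-lowering treatment.
- **What is collected** (same section): an itemised blood panel with FPG and four lipids (TC, TG, LDL-C, HDL-C); medical history of hypertension, diabetes and hyperlipidemia; and current drugs, including statins, insulin and hypoglycemic medicine. Table 1 (Follow up) ticks laboratory examination at baseline only.
- **Role of these variables**: Aim 1 is to show that BVHS predicts MACEs independently of traditional risk factors. The Background says "traditional risk factors are not included in BVHS, but are used as adjusted confounding factors". Statistical analysis methods, however, adjusts the Cox model for variables that may be imbalanced at baseline and names no set.
- **What was found** (Results): "dyslipidemia was observed in 41.7% and 37.4% were on medication of statins". Table 2 gives the counts as 687 and 615, with 1648 enrolled.

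**The concern.** The definitions and the data list stand next to each other in one section and do not match. Some criteria have no listed measurement behind them. One asks for repeated values from a single scheduled test. The recorded history, which is available, is not used. As written, a person with diagnosed but untreated diabetes and an FPG below 7.0 mmol/L is classed as non-diabetic.

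The reported dyslipidemia count is only slightly larger than the number of statin users. That is unexpected for a definition with several separate lipid thresholds, and it raises the question of whether this definition produced Table 2.

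Aim 1 is at stake. If diabetes or lipid disorder is under-recorded and is more common where vascular grades are worse, part of its effect stays with BVHS after adjustment. The looser the rule for choosing covariates, the less certain it is that the measured lipids and glucose enter the model and limit this.

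**Working it through.** **Step 1. Criteria against listed data.**

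| Criterion | Listed baseline source | Usable as planned |
|---|---|---|
| HbA1c ≥ 6.5% | none | no |
| FPG ≥ 7.0 mmol/L | FPG | yes |
| 2-hour glucose ≥ 11.1 mmol/L | none | no |
| Glucose-lowering treatment | drug list | yes |
| History of diabetes | collected | not in the definition |
| TC, LDL-C, HDL-C thresholds | all three measured | yes |
| Lipoprotein(a) | none | no |
| Persistent TG elevation | one TG value | single value only |
| Lipid-lowering treatment | statins named, no other lipid drug | statins only |
| History of hyperlipidemia | collected | not in the definition |

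Each definition keeps working criteria. What is lost is sensitivity.

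**Step 2. Table 2 against the definition.** Inputs from Results and Table 2: N = 1648, dyslipidemia 687, statin users 615.

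- 687/1648 = 41.69%, which reproduces the printed 41.7%.
- 615/1648 = 37.32%, which rounds to 37.3%, not the printed 37.4%. A denominator of 1643 to 1646 would give 37.4%, so a few missing values could explain it.
- By definition all 615 statin users are positive. Positives left among non-users: 687 − 615 = 72. Non-users: 1648 − 615 = 1033. Share: 72/1033 = 7.0%.

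Since 687 exceeds 615, nothing is arithmetically impossible. The documents give no lipid prevalence to set beside the 7.0%. As a what-if only, let a share s of non-users meet a criterion; the expected count is 615 + s × 1033:

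| Assumed s | Expected count | % of 1648 |
|---|---|---|
| 10% | 718 | 43.6 |
| 20% | 822 | 49.9 |
| 30% | 925 | 56.1 |
| 40% | 1028 | 62.4 |
| 50% | 1132 | 68.7 |

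The reported count is 687 (41.7%). It fits the definition only if s is about 7%.

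**Step 3. How much missed diabetes could matter.** All inputs are assumptions: hazard ratio of diabetes HR = 1.5 to 2.0; prevalence p = 25% to 30% in the high and 15% in the low BVHS group; a share d = 60% to 90% of diabetics detected. In the stratum labelled non-diabetic, the fraction of missed cases is m = p(1 − d)/(1 − p·d). The spurious risk ratio is [1 + m_high(HR − 1)]/[1 + m_low(HR − 1)].

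- Mildest case (HR 1.5, 25% against 15%, d = 0.9): m_high = 0.025/0.775 = 0.032; m_low = 0.015/0.865 = 0.017; ratio = 1.016/1.009 = 1.01.
- Strongest case (HR 2.0, 30% against 15%, d = 0.6): m_high = 0.12/0.82 = 0.146; m_low = 0.06/0.91 = 0.066; ratio = 1.146/1.066 = 1.08.

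Sample size calculation assumes a risk ratio of 1.94 for BVHS, so a distortion of 1.01 to 1.08 is small beside it.

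**Step 4. Room for adjustment.** Incidence of end point events expects 1500 × 30/1000 = 45 events. Age, sex, smoking, SBP, TC, HDL-C, FPG and three treatment indicators make 10 terms. With one BVHS term that is 11, or 45/11 = 4.1 events per term. The set therefore has to be short and chosen in advance.

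**The case against.** The strongest reply is that the criteria are joined by an either-or. FPG, four lipids, statins, glucose-lowering drugs and history are all collected, so an unmeasured alternative costs some sensitivity and does not leave a variable undefined. This stands. The item lists also come from a condensed article and need not be exhaustive, although a panel that runs to individual cardiac enzymes and sits directly before the definitions makes an accidental omission less likely.

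A reader might infer more, and the documents do not support it:

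- **That the 687 is wrong.** This needs a lipid prevalence that the documents do not give. Table 2 says dyslipidemia and the definition says hyperlipidemia, so Table 2 may rest on another basis, such as history. Any number of misclassified people is an assumed share of the non-users minus 72, not evidence.
- **That the comparator scores are handicapped.** The article does not give the inputs of China-PAR or the Pooled Cohort Equations. Its generic list in the Discussion uses measured TC and HDL cholesterol, which are collected, and no binary lipid label.
- **That family history is missing from the study.** The Discussion lists "obesity, diabetes mellitus and family history of premature CVD or coronary heart disease (CHD") among the factors that most models use. This does not set the study's own confounders, and the questionnaire is not shown.
- **That the bias certainly favours BVHS.** This is the plausible direction for an under-recorded factor that tracks vascular damage. It is not a documented result.

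**Conclusion.** The point holds in a limited form. The two definitions include criteria that the listed data cannot supply and leave out history that the study records. Table 2 leaves at most 72 of 1033 non-users of statins (7.0%) positive, which calls for an explanation but contradicts nothing. Residual confounding of Aim 1 is possible, plausibly in favour of BVHS, and probably small: 1.01 to 1.08 in the diabetes illustration, which rests wholly on assumed prevalence, hazard ratio and detection. The weaker part of the plan is the adjustment rule. Choosing covariates by baseline imbalance does not ensure adjustment for the traditional risk factors that Aim 1 names. The change is worth making because it uses data already collected.

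**What to change.** 1. For the analysis, define diabetes as FPG ≥ 7.0 mmol/L, glucose-lowering medication or recorded history. Define hyperlipidemia from measured baseline TC, LDL-C, HDL-C and TG, medication or recorded history. Drop the criteria that were not collected and the word persistent.
2. State which definition produced the 687. If it differs from item 1, recompute Table 2, and check the statin percentage or state its denominator.
3. In the Cox model for Aim 1, replace adjustment for imbalanced variables with a fixed, parsimonious set of traditional risk factors, named before the events are analysed. Enter SBP, lipids and FPG as continuous values with treatment indicators, and size the set to about 45 expected events.
4. If family history was not collected at baseline, report that as a limitation. Do not collect it after events have occurred: all-cause death is part of MACEs, so missingness would depend on the outcome, and people who have had an event may recall differently.

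The cost is a little recoding of data already in the EDC. The BVHS effect may look slightly smaller.
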